#### Provisions for post-trial care {30}

At the end of the intervention and surgery, participants will be extubated the DLT in the operating room and sent to the PACU for observation (or to the ICU with the DLT if the patient is in poor condition) and then sent back to the ward. There are risks associated with thoracic surgery and DLT intubation. Regardless of the reason for any adverse events, our department and the hospital will offer care.

### Outcomes {12}

#### Primary outcome

The incidence of DLT malposition observed via the FOB in lateral and supine intubation groups. The definition of DLT malposition is that the DLT is moved to correct its position by more than 1.0 cm [9].

#### Secondary outcomes

The time of intubation. Defined as the time from the use of the video-laryngoscope to confirm the correct position of the DLT by using the FOBThe frequency and duration of re-adjustments under FOBWhether to re-intubateIntraoperative vital signs, including heart rate, blood pressure and oxygen saturationPostoperative recovery, including early postoperative complications and the Quality of Recovery-15 (QoR-15) questionnaire at 24 h after surgery

In designing this trial, we aim to explore the effect of lateral intubation after induction on the position of DLT in patients undergoing elective unilateral VATS. In order to visually and quantitatively measure the effect, the rate of DLT movement of more than 1.0 cm observed via the FOB will be compared between lateral intubation and supine intubation. This definition of DLT malposition was also used in the study by Inoue et al. as the authors indicated that Japanese patients were small and a deviation of 1.0 cm could be significant for them [9]. In China which is also in Asia, the DLT movement more than 1.0 cm is also critical for Chinese patients, so we select the deviation of 1.0 cm as the cut-off value.

For information on how to measure the distance of DLT movement, we refer to Desiderio et al. [8] on the method of measuring tracheal distance. After the DLT positioning is completed, the distance from the main carina to the distal tip of the tracheal lumen is measured in centimeters using the FOB as the carina-to-tracheal distance. Specifically, it is the difference between the depth when the tip of the FOB is at the main carina minus the depth when the tip of the FOB is at the distal tip of the tracheal lumen. The carina-to-tracheal distance measured after accurate DLT positioning is taken as the base value, and then measured again after turning to the lateral position or intraoperatively, a difference of more than 1.0 cm from the base value is recorded as DLT malposition.

#### Participant timeline {13}

The participant timeline is shown in Fig. 1.

**Fig. 1 Fig1:**
[figure not shown]
Time schedule of enrolment, interventions, assessments, and visits for participants. DLT, double-lumen tube; QoR-15, Quality of Recovery-15 questionnaire

#### Sample size {14}

This trial focuses on whether intubation in the lateral position under general anesthesia will reduce the DLT malposition rate observed via the FOB in patients proposed for unilateral VATS; therefore, the expected sample size is calculated based on the current DLT malposition rate. According to previous studies, the incidence of DLT malposition is about 30% [9]. Expecting a 50% reduction in malposition rate to be considered an effective intervention, we chose *α* = 0.05 and test efficacy *β* = 80%, which is calculated to yield 48 cases in each group by using the PASS 15.0 software. Considering a 10% drop-out rate, the final sample size is derived as at least 54 cases per group, with a total of 108 patients included.

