### Assignment of interventions: allocation

#### Sequence generation {16a}

The computerized random number generator is used to generate random sequences on a 1:1 basis, and the random sequence will be put into a sealed, opaque and sequentially numbered envelope by the investigator. When the participant is admitted to the operating room the investigator will open the envelope to obtain a random sequence to determine the grouping. Participants with random sequences 1–54 are assigned to group L, while 55–108 are assigned to group C. Each participant will be given a unique study sequential number on the envelope cover in the order of their participation in this study. The random sequences of all participants and its corresponding study sequential numbers will be recorded in the randomization list.

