### Statistical methods

#### Statistical methods for primary and secondary outcomes {20a}

The SPSS statistical software version 26.0 (IBM) will be used for statistical analysis. Primary and secondary outcomes will be analyzed as follows: use Kolmogorov–Smirnov test to determine whether continuous data follows normal distribution. Continuous data following a normal distribution are expressed as mean ± standard deviation (‾x ± s), while nonnormal distributions are expressed as median (quartile spacing). The independent samples *t* test will be used for comparison between groups of normally distributed continuous data. The Mann–Whitney *U* test will be used for comparison of non-normally distributed continuous data. Count data are expressed as number of cases (rate) and tested by chi-square test or Fisher’s exact test. If subsequent multi-factor analysis will be required, multiple linear regression or logistic regression models are selected according to continuous-type or sub-type dependent variables. The data analysis of this study adopts the principle of intentional analysis. Multiple interpolation will be used for the analysis of missing data, and sensitivity analysis will be performed. Probability values < 0.05 will be considered significant.

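### The stated 48 per group does not give 80% power for 30% versus 15%: about 121 per group are needed, and the planned size has about 42–46% power

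*Protocol article*

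**What the plan says.** Section {14} of the protocol article takes a malposition rate of about 30% from a previous study and sets the target effect: "Expecting a 50% reduction in malposition rate to be considered an effective intervention". It sets alpha at 0.05 and power at 80% (written there as a value of β), and gives the result: "which is calculated to yield 48 cases in each group by using the PASS 15.0 software". An allowance of 10% for drop-out brings this to at least 54 per group, 108 in total.

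The trial has two parallel groups with 1:1 allocation (Trial design {8} and Sequence generation {16a}). The primary outcome is binary. Under {20a}, count data are "tested by chi-square test or Fisher’s exact test", and the only decision rule is "Probability values < 0.05 will be considered significant". Neither section says whether the test is one-sided or two-sided.

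**The concern.** Detecting 30% versus 15% with 80% power normally takes well over 100 patients per group, so 48 looks too small by a factor of more than two. The section gives the control rate, the effect, alpha, power and the resulting number, so the result can be checked against its own inputs.

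This calculation is the only justification given for the size of the trial, and it concerns the primary outcome. If the power claim is wrong, a reader who trusts it could take a non-significant result as evidence against a halving of malposition, when the trial had less than an even chance of detecting one. No interim analysis is planned ({21b}), so no planned look at the data would reveal the shortfall.

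**Working it through.** **Inputs.** Control rate p1 = 0.30. A 50% reduction gives p2 = 0.15; it must be relative, since a 50-point fall from 30% is impossible. Alpha = 0.05, power = 0.80 and 1:1 allocation are from {14} and {16a}. Two-sided testing is an assumption, so one-sided results are shown as well.

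**Attempt to reproduce 48.** Pooled-variance formula for two proportions, with mean rate 0.225:

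n = [z_α·√(2·0.225·0.775) + z_β·√(0.30·0.70 + 0.15·0.85)]² / 0.15²

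- Two-sided: [1.96·√0.34875 + 0.8416·√0.3375]² / 0.0225 = (1.1575 + 0.4889)² / 0.0225 = 120.5, so **121 per group**.
- One-sided: [1.645·√0.34875 + 0.8416·√0.3375]² / 0.0225 = (0.9714 + 0.4889)² / 0.0225 = 94.8, so **95 per group**.

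Other standard two-group variants, per group:

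| Formula | Two-sided | One-sided |
|---|---|---|
| Pooled | 121 | 95 |
| Unpooled | 118 | 93 |
| Arcsine | 119 | 94 |
| Continuity-corrected | 134 | 108 |

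None comes near 48. The drop-out step is right (48/0.9 = 53.3, rounded up to 54), so the error lies in the 48 itself.

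**Power at the planned size, 30% versus 15%.** For n = 48 two-sided: the standard error under the null is √(0.34875/48) = 0.0852 and under the alternative √(0.3375/48) = 0.0839, so power = Φ[(0.15 − 1.96·0.0852)/0.0839] = 41.9%. The exact figures enumerate all binomial outcomes.

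| | 48 per group | 54 per group |
|---|---|---|
| Two-sided, normal approximation | 41.9% | 46.2% |
| Two-sided, exact, uncorrected chi-square | 42.6% | 46.9% |
| Two-sided, exact, Fisher | 33.4% | 37.4% |
| One-sided, normal approximation | 54.6% | 58.9% |

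**What the planned size can detect.** Solving the same two-sided formula for 80% power against a 30% control rate gives p2 = 7.9% at 48 per group (a reduction of 1 − 7.9/30 = 74%) and 8.9% at 54 (1 − 8.9/30 = 70%). These values apply to the chi-square test; by exact enumeration, Fisher's test has only about 74% power at each of them. To detect a halving with 80% power, the control rate would have to be about 56% at 48 per group or 52% at 54.

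**Precision.** The expected 95% half-width for the risk difference at 30% versus 15% is 1.96·√(0.3375/n): 16.4 percentage points at 48 per group and 15.5 at 54.

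**The case against.** Five points can be made for the plan.

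- **A one-sided test may have been meant**, since the hypothesis is directional. This does not rescue the figure: at least 93 per group are still needed, and power is 55–59%. It does mean that the statement that a true halving would more likely than not be missed holds only for a two-sided test.
- **All 54 per group may be analysed**, because {20a} adopts intention-to-treat and imputation. That is fair: 42% applies after the assumed drop-out and 46% without it. Both are far below 80%.
- **The control rate may be higher than 30%.** The Background cites 26–37% as the main range. At 37% versus 18.5%, two-sided power is 53% (n = 48) or 58% (n = 54). The Background also cites 25–54% after bronchoscopic assessment, and at 54 per group the required 52% falls inside that range, but only near its top. The plan is built on 30%.
- **The figure came from established software.** Naming the software does not make 48 follow from the stated inputs. An input may have been entered or transcribed differently. A one-sample, one-sided test against a fixed 30% gives about 49, and a one-sided 95 read as a total and halved gives 48. Neither fits this design, and neither origin can be shown from the document.
- **The protocol does not say that a non-significant result would be read as no benefit.** That is correct. It is a risk created by an overstated power with a p-value rule, not something the plan prescribes.

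These points affect how the shortfall is described. None removes it.

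**Conclusion.** The concern holds. The 48 per group does not follow from the inputs in {14} by any standard two-group formula tried, and the 80% power claim is false. For 30% versus 15% at two-sided 0.05, the trial needs about 121 evaluable per group, some 2.5 times the stated number (121/48). As planned it has about 42% power with 48 evaluable per group and about 46% with all 54, and less with Fisher's test. The exact percentages assume a two-sided test and rates of 30% and 15%. The conclusion that 80% is not reached does not depend on sidedness or on whether 48 or 54 are analysed. The claim has to be corrected because the size of the trial rests on it.

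**What to change.** Correct {14}:

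- Withdraw the statement that 48 per group is enough for a 50% reduction, state whether the test is one-sided or two-sided, and write 80% as power (1 − β).
- If 108 patients are kept, state that 54 per group (48 evaluable) gives about 42–47% power for 30% versus 15% with a two-sided uncorrected chi-square test (33–37% with Fisher's exact test), and that 80% power applies only to a fall to about 8–9% with the chi-square test.
- If the calculation used other inputs or another procedure, disclose and justify them.

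This is a wording amendment. It needs no extra patients, but it makes the stated power less favourable and leaves the trial underpowered for the effect it calls effective.

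The alternative is to keep the 80% claim and enlarge the trial: 121 per group, or 121/0.9 = 134.4, so 135 per group and 270 in total with 10% drop-out. That is 162 more patients than planned (270 − 108).

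If the size stays at 108, it would also be sensible, though not required to correct the error, for {20a} to make the risk difference with its 95% confidence interval the main result (expected half-width about 15–16 points) and to say that a non-significant result will be reported as inconclusive.

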#### Recruitment {15}

Study participants will be recruited from patients undergoing unilateral VATS at Huzhou Central Hospital. The research team including anesthesiologists and thoracic surgeons will involve in the recruitment process. There is an adequate source of patients to ensure the number of enrollment, and 4 months is enough to complete the enrollment of 108 eligible participants. Currently, this trial is in the recruitment phase and patients will be screened strictly according to the recruitment criteria.

### Assignment of interventions: allocation

#### Sequence generation {16a}

The computerized random number generator is used to generate random sequences on a 1:1 basis, and the random sequence will be put into a sealed, opaque and sequentially numbered envelope by the investigator. When the participant is admitted to the operating room the investigator will open the envelope to obtain a random sequence to determine the grouping. Participants with random sequences 1–54 are assigned to group L, while 55–108 are assigned to group C. Each participant will be given a unique study sequential number on the envelope cover in the order of their participation in this study. The random sequences of all participants and its corresponding study sequential numbers will be recorded in the randomization list.

#### Concealment mechanism {16b}

The random sequence, study sequential number and group allocation of participant will be typed onto separate pages and be collected to store confidentially. The randomization process will be performed by investigators who are not involved in postoperative follow-up and data analysis.

#### Implementation {16c}

The randomization stated above will decide the allocation of intubation position (lateral versus supine). Participants enter the operating room to be determined the grouping, then the investigator will inform the participant of the specific grouping and assist the participant in lateral or supine position. The principal investigator will prepare the envelope with random sequence for allocation.

### Assignment of interventions: blinding

#### Who will be blinded {17a}

This study is an open-label clinical trial. It is not possible to blind participants, anesthesiologists, and surgical team when the intervention is implemented in this trial. But for researchers in postoperative follow-up and data analysis, they will not know the allocation of participants.

#### Procedure for unblinding if needed {17b}

Unblinding will not occur because this study is an open-label clinical trial.

#### Plans to promote participant retention and complete follow-up {18b}

Considering that the intervention may not have long-term effects on participants, we will only perform the follow-up at 24 h postoperative. When obtaining informed consent, we will explain to the participant that there will be a brief questionnaire for 3–5 min and stress the importance of this.

#### Data management {19}

All participant data collected in this study will be processed in accordance with the Data Security Law of the People’s Republic of China. All participant data will be manually filled in the paper CRFs and then transcribed into Microsoft Excel by the researcher not involved in the implementation of the intervention. Primary monitoring will be performed by an independent research nurse, including checking all preoperative, intraoperative, and postoperative CRFs and informed consent forms for missing items, incorrect filling, and illegible writing. The coordinator will review all errors and verify that the errors are crossed out and finally annotated with a signature and date. In accordance with local and national regulations, raw data such as paper CRFs will be stored in a locked cabinet in the anesthesiology office that can only be opened by authorized personnel. Data entered into Microsoft Excel will be securely stored on a password-protected desktop computer in the locked office. Access is restricted to investigators assigned to data entry, processing, and analysis.

#### Confidentiality {27}

The randomization list and paper CRFs will be kept in a locked cabinet in the anesthesiology office under the supervision of the principal investigator. Considering that the paper CRFs contain participant names and study sequential numbers, access to the paper CRFs will be authorized only upon special request and after strict review, for the protection of participant privacy. De-identified data will be entered into Microsoft Excel, access codes will be set and stored on a locked computer, and only authorized investigators will have access. Any subsequent publications will not include any patient identifying information and study sequential numbers.

#### Plans for collection, laboratory evaluation, and storage of biological specimens for genetic or molecular analysis in this trial/future use {33}

Not applicable, there will be no biological specimens collected.

### Statistical methods

#### Statistical methods for primary and secondary outcomes {20a}

The SPSS statistical software version 26.0 (IBM) will be used for statistical analysis. Primary and secondary outcomes will be analyzed as follows: use Kolmogorov–Smirnov test to determine whether continuous data follows normal distribution. Continuous data following a normal distribution are expressed as mean ± standard deviation (‾x ± s), while nonnormal distributions are expressed as median (quartile spacing). The independent samples *t* test will be used for comparison between groups of normally distributed continuous data. The Mann–Whitney *U* test will be used for comparison of non-normally distributed continuous data. Count data are expressed as number of cases (rate) and tested by chi-square test or Fisher’s exact test. If subsequent multi-factor analysis will be required, multiple linear regression or logistic regression models are selected according to continuous-type or sub-type dependent variables. The data analysis of this study adopts the principle of intentional analysis. Multiple interpolation will be used for the analysis of missing data, and sensitivity analysis will be performed. Probability values < 0.05 will be considered significant.

#### Interim analyses {21b}

Not applicable, no interim analyses are planned.

#### Methods for additional analyses (e.g., subgroup analyses) {20b}

Not applicable, no additional analyses are planned.

#### Methods in analysis to handle protocol non-adherence and any statistical methods to handle missing data {20c}

Given that we will explain the intervention in detail and emphasize cooperation matters to the patient during pre-anesthesia evaluation and obtaining informed consent, we guess that few patients will protocol non-adherence. If needed, multiple interpolation will be used for the analysis of missing data, and sensitivity analysis will be performed.

#### Plans to give access to the full protocol, participant level-data, and statistical code {31c}

This is a principal investigator-initiated trial. Access to the full protocol and participant level data will be considered upon submission of a reasonable request and consent of the principal investigator.

### Oversight and monitoring

#### Composition of the coordinating center and trial steering committee {5d}

This is a single-center trial. No steering committee will be formed. Weekly group meetings will be initiated by the principal investigator to discuss the progress of the study.

#### Composition of the data monitoring committee, its role and reporting structure {21a}

We expect the rapidly inclusion of 108 participants and plan to complete the trial within 4 months; therefore, no data monitoring committee will be formed.

#### Adverse event reporting and harms {22}

Adverse events that occur in this trial will be recorded on the CRF and reported to the principal investigator.

Each adverse event will be assessed for the character (expected vs unexpected), severity (serious vs non-serious), and relevance to the intervention (relevant vs irrelevant). Serious and unexpected adverse events will be reported to the Ethics Committee. The principal investigator will conduct regular cumulative reviews of all adverse events and convene investigator meeting as necessary.

#### Frequency and plans for auditing trial conduct {23}

A research nurse who is not involved in the current trial will act as an independent reviewer for the duration of the trial. The audit process takes place every 2 weeks by the independent research nurse, and all errors will be recorded and reported to the principal investigator. The audit process will include a review of CRFs, registries, missing data, duplicate data, and informed consent documentation.

#### Plans for communicating important protocol amendments to relevant parties (e.g., trial participants, ethical committees) {25}

The Ethics Committee of Huzhou Central Hospital has reviewed the protocol and agreed to conduct the trial as the protocol. No protocol amendments will be made unless permitted by the Ethics Committee. Any important protocol modifications will be reviewed by the principal investigator who will sign the amendment, which will be submitted to the ethics committee for approval later.

#### Dissemination plans {31a}

Following statistical analysis of the trial, every endeavor will be made to publish the results in peer-reviewed journals related to clinical anesthesia and thoracic surgery.

## Discussion

There are many reasons for DLT malposition in thoracic surgery, especially shifting the patient from supine to lateral position which may lead to more malposition [8]. Several innovative approaches by many researchers have shown promising results in reducing the incidence of DLT malposition during lateral positioning. For example, it has been shown that the DLT malposition rate was lower in patients who removed the headrest before lateral positioning compared to those who used the headrest all the time [22]. In addition, one study found that limiting head and neck movements with a neck brace also minimized DLT malposition during supine to lateral position [7]. Unfortunately, these effective measures did not fundamentally solve the DLT malposition caused by the patient’s position change. We expect that the lateral intubation after assisting the patient to a comfortable and surgically required lateral position before induction will thoroughly resolve the DLT malposition or other adverse effects caused by lateral positioning. Of course, there is more than one cause for the malposition. All occurrences of DLT malposition will be recorded throughout the trial, as well the time and the possible reason.

For anesthesiologists who have never tried or even heard of lateral DLT intubation, this procedure seems awkward and difficult. However, based on our preliminary pre-experiments, this process is not as challenging as anticipated when using flexible intubation techniques and proper DLT shaping. After intubation in the lateral position, the patient does not need to be moved again and the operation can be started directly. It reduces the need for medical staff to shift position of patient under anesthesia, which is an unsafe and labor-intensive process, so the lateral DLT intubation is well received by operating room nurses and surgeons. The results of the study, we anticipate, will provide evidence for the clinical application and efficacy of lateral intubation, pioneering a new approach to DLT intubation in thoracic surgery.

